### **6.5.1 Follow up of participants 'off protocol'**

"Off protocol" is defined as: study participants who commence aspirin therapy or cease trial medications on clinical grounds or because of a lack of preparedness to continue in the study.

Regardless of the decision to continue with the study medication, the participant will be asked to attend all scheduled follow-up visits as if they were maintaining full participation. Those who are unwilling to do this will be asked if they will agree to phone call/mail follow-up and, in addition, for approval to continue follow-up through surveillance of their clinical records (or just the latter, if they are unwilling to be contacted in any form). Those who refuse all forms of follow-up will have their outcomes assessed in the national morbidity and mortality databases. All participants will be asked to provide approval for access to this information as part of the study enrollment procedures. In all cases where a participant ceases taking their study medication, the reason for discontinuation, the date of discontinuation and date of the last dose of study medication, should be recorded.

### **6.5.2 Anemia diagnosed in a study participant**

Hemoglobin results will be provided to the usual treating physician on an annual basis as part of

the annual follow-up report for the participant. The treating physician will be advised to follow their routine clinical practice for the management of patients with anemia. When the cause of the anemia is determined to be blood loss and when the cause of blood loss is identified (e.g. a bleeding colonic polyp), encouragement will be given to recommence the trial drug once the underlying cause is treated. Similarly, physicians may choose to advise participants to recommence their study medication if the anemia has responded to therapy such as iron replacement.

### **6.5.3 Major surgery**

Participants will be advised to contact the research staff or research clinic when any surgery is planned. Their physician will be advised to treat the participant as if they are taking aspirin and that the participant may temporarily cease the trial drug if they consider it advisable. No unblinding will occur. Participants will be encouraged to recommence study medication at a time determined by the participant's surgeon in consultation with their usual treating physician.

### **6.5.4 Major bleed**

Participants will be advised to cease randomized study medication on diagnosis of a non-traumatic major hemorrhage, e.g. a bleeding peptic ulcer. The participant will be followed for the duration of the study. [Such a trial medication cessation may be temporary or permanent depending on the condition and the clinical judgment of the physician or surgeon.](#)

Gastrointestinal hemorrhages or hemorrhages at other sites that required transfusion, hospitalization, prolonged hospitalization, surgery or are fatal will be considered as clinically significant bleeding. Source information from clinical case notes and hospital medical records related to these events will be collected and sent to the ASPREE Data Management Center. A clinically significant bleed may lead to temporary or permanent trial medication cessation, according to the treating physician or surgeon's clinical judgment, but not exit from the trial. There is no standard accepted clinical trial definition of major gastrointestinal bleed in Australia. Our operating definition has been accepted by the Australian Gut Foundation.

### **6.5.5 Abdominal discomfort/dyspepsia**

Participants will be advised to discuss abdominal discomfort / dyspepsia with their usual treating physician. Both physician and participant will be advised that the ASPREE pilot studies suggest that only 20% of such symptoms are likely to be due to the active trial drug. If symptoms are persistent the recommendation will be to cease the study medication for a trial period and then re-challenge. If symptoms recur then the physician may add other medication (e.g. a proton

pump inhibitor) or cease the trial drug. The participant will be asked to continue in the trial.

#### **6.5.6 Commencement of regular non-steroidal medication (NSAID)**

Participants will be advised to avoid continuous NSAID use. Additional advice to physicians and participants is that treatment with NSAIDs (including aspirin) should be at the lowest dose and for the shortest period possible for clinical effectiveness. Details of all NSAID use and duration will be recorded.

#### **6.5.7 Development of an indication for aspirin**

Participants who develop a recognized clinical indication for continuous use of aspirin may commence routine aspirin and will continue in the study for observation of endpoints.

#### **6.5.8 New diagnosis of diabetes**

All participants will be advised to discuss a new diagnosis of diabetes with their usual treating physician. The decision to cease the study medication and commence active aspirin will be made by the physician in consultation with their patient. The participant will be asked to continue with routine follow-up visits.

#### **6.5.9 New diagnosis of atrial fibrillation**

To aid in the detection of undiagnosed chronic atrial fibrillation (AF), during the annual visit research staff will check the participant for an irregular pulse, either by palpation or by failure of the automated blood pressure instrument to collect a reading. If the annual visit takes place in a clinic, most clinics will then run an ECG to determine if the irregular rhythm is non-pathological (e.g. due to multiple ectopics). If AF is detected (confirmed by the clinic physician), the participant will be referred to their usual primary care clinic or doctor and will cease study medication. In the event that visits do not take place in the clinical setting (mostly in Australia), or there is no access to an ECG machine, the participant will be referred directly to the primary care doctor or general practitioner for diagnosis and further investigation if required.

#### **6.5.10 Commencement of warfarin or other antiplatelet drugs**

A prescription of warfarin, aspirin or other anti-thrombotic drug will be reason for stopping study medication but the ASPREE participant will continue to be followed for the duration of the study. If warfarin or other anti-thrombotic drug is prescribed for a limited period (such as for DVT), study medication will be ceased for that period, but may be resumed after anti-thrombotic therapy has been stopped.

### **6.5.11 Commencement of aspirin on own volition**

Participants entering the study will be provided with information about the need to avoid chronic self medicated aspirin therapy. At each annual visit, the participant will be asked whether there has been a change in their chronic drug use, including aspirin use, and, if so, will be asked to discuss this with their doctor and encouraged to avoid chronic aspirin use.

The participant will be reminded of this requirement at annual follow-up visits and through the trial newsletter and other communications. Although it will be discouraged, participants are entitled to commence aspirin if they so choose. Regardless, all randomized subjects, whether continuing with randomized treatment or not, will be followed in an identical fashion for the duration of the trial.

In Australia, the participant's usual treating physician is a co-investigator and is unlikely to recommend low dose aspirin without a recognized clinical indication. Participants will also be given cards to carry in their wallets to show other health care providers, and are educated on the forms of aspirin that are on the market.

## **7 MEASUREMENTS, CRFs AND ANALYTICAL METHODS**

### **7.1 Schedule of study visits**

The trial is primarily designed to assess mortality and morbidity although other measures will be determined. The ASPREE Measurement and Study Activity schedule for each of the study visits is summarized in Table 4.

#### **7.1.1 Lifestyle Profile and Screening visit (Visit 1)**

Measurements and data will be collected by the research staff after the participant has provided informed consent to participate in the study. Each study participant will be assigned a unique identification number, which will be used throughout the study. The information to be collected at this visit (and thereafter at some or all Annual Visits\* - see Table 4) includes:

- a) Basic demographic and lifestyle factors including living situation\*, ethnicity and language, personal medical history\*, smoking history\*, alcohol use\*, medication history\* and level of education.
- b) Family history of acute MI, stroke, renal disease, colorectal and other cancers, or dementia – identified by the participant and from medical case notes.

- c) Blood pressure and heart rate\*: measured in the seated position following 5 minutes of rest using an oscillometric device. The average of three measurements taken 1 minute apart will be recorded.
- d) Cognitive function\* and depression: assessed using the Modified Mini-Mental State Examination (3MS) score  and the Center for Epidemiologic Studies – Depression 10 (CES-D)  questionnaires. The 3MS will be implemented as part of the screening of participants (where the score will be used to determine eligibility for the study) and will be administered again at years 1, 3, 5 and 7. The CES-D is a self-administered questionnaire used to screen for depression. It will be used in association with the 3MS, as depression is a confounder for cognitive function ascertainment, and also to ascertain new onset depression.
- e) Physical disability\*: assessed by the participant's self-reported ability to perform the 6 Katz Activities of Daily Living (ADLs), which form a component of the Lifestyle Interventions and Independence for Elders (LIFE) Disability questionnaire.
- f) Referral to a local Pathology Provider (in Australia) or direct collection of a fasting blood sample\* (~12 ml, for the measurement of total cholesterol, LDL-C, HDL-C, triglycerides, glucose, creatinine and hemoglobin) and urine spot test (minimum of 20 ml, to measure the albumin : creatinine ratio and detect the presence of microalbuminuria). Where available, a point-of-care instrument will allow prior screening for low hemoglobin levels.
- g) Placebo medication for the run-in phase of 4 weeks will be dispensed to enable subsequent determination of medication compliance during this period.
- h) Review of inclusion / exclusion criteria.

| Measurement/
Activity                | Lifestyle
Profile &
Screening
(Visit 1) | Assess-
ments &
Eligibility
(Visit 2) | Follow
-up
(1yr) | Follow
-up
(2yr) | Follow
-up
(3yr) ** | Follow
-up
(4yr) ** | Follow-
up
(5yr)** | Follow-
up
(6yr)** | Follow
-up
(7yr)** |
|-------------------------------------------------|----------------------------------------------------------------|--------------------------------------------------------------|---------------------------------|---------------------------------|------------------------------------|------------------------------------|-----------------------------------|-----------------------------------|-----------------------------------|
| Review inclusion/
exclusion criteria | X                                                       | X                                                     |                                 |                                 |                                    |                                    |                                   |                                   |                                   |
| Obtain informed consent                  | X                                                       |                                                              |                                 |                                 |                                    |                                    |                                   |                                   |                                   |
| Dispense study
medication            | X (Run-In
only)                                     | X                                                     | X                        | X                        | X                           | X                           | X                          | X                          | X                          |
| Assess medication
compliance         |                                                                | X                                                     | X                        | X                        | X                           | X                           | X                          | X                          | X                          |

|                                                                                                                                                                                      |                 |                 |                 |                 |                 |                 |                 |                 |                  |
|--------------------------------------------------------------------------------------------------------------------------------------------------------------------------------------|-----------------|-----------------|-----------------|-----------------|-----------------|-----------------|-----------------|-----------------|------------------|
| Concomitant medications                                                                                                                                                       |                 | X               | X               | X               | X               | X               | X               | X               | X                |
| Blood pressure & heart ratea, heightb, weightc & abdominal circumferencec                                                 | X a  | X bc | X ac | X ac | X ac | X ac | X ac | X ac | X abc |
| Demographics, family & personal history & lifestyle factors                                                                                                           | X               |                 | X               | X               | X               | X               | X               | X               | X                |
| Laboratory testing:
- Fasting blood: total cholesterol, HDL, LDL, triglyceride, glucose, creatinine & hemoglobin
- Urine: albumin:creatinine ratio and microalbuminuria | X               |                 | X               | X               | X               | X               | X               | X               | X                |
| Quality of Life
- SF-12                                                                                                                                                    |                 | X               | X               | X               | X               | X               | X               | X               | X                |
| Assess cognitive function & depression
- 3MS a , CES-D b SDMT c HVLT-R c & COWAT c                              | X ab | X c  | X               | X b  | X               | X b  | X               | X b  | X                |
| Assess physical disability
- KATZ ADLs                                                                                                                                     | X               |                 | X               | X               | X               | X               | X               | X               | X                |
| Assess physical function
- Walk test and grip strength                                                                                                                     |                 | X               |                 | X               |                 | X               |                 | X               | X                |
| Clinical event reporting
- Questionnaire & medical record review                                                                                                           |                 | X               | X               | X               | X               | X               | X               | X               | X                |
| Retinal Imaging^                                                                                                                                                   |                 | X               |                 |                 | X               |                 |                 |                 |                  |

**Table 4. ASPREE Measurement and Study Activity Schedule**

(X indicates that all measures are carried out except where superscripts a,b,c indicate those tests that are the only ones performed at the designated time point.) \*\* Final annual visit will take place in years 3, 4, 5, 6 or 7 depending on year of randomization. Final visit measurements will be the same as those indicated for year 7.

**Telephone calls** will also take place in between annual visits for purposes of retention and for clinical event reporting. A person-to-person call will occur in the U.S. 4 weeks after Visit 2, automated or person-to-person calls will occur at 3 and 9 months and direct person-to-person calls will occur at 6 months between annual face-to-face visits. At the 6 month call, participants will be asked specifically about all endpoints and will be administered the Katz ADL's.

^ Retinal Imaging will only be conducted on participants in Melbourne or other locations in Australia subject to the availability of imaging equipment.

### **7.1.2 Post screening visit study activity (Run-in phase between Visits 1 & 2)**

Following the screening visit, blood samples will be collected by the local Pathology laboratory provider (in Australia). Laboratory pathology results will be available to the study site within the first two weeks in the run-in phase of the study. These results will be used to satisfy inclusion and exclusion criteria. In Australia, the participant will also consult his / her family physician during this run-in phase, whereupon the family physician will complete the GP

### **7.1.3 Determinations at Eligibility and Assessments visit (Visit 2)**

At the end of the 4 week run-in phase, the 'Assessments & Eligibility visit' (Visit 2) will take place. At this visit (and, unless stated otherwise, at every Annual Visit) the following measurements and study activities will be conducted:

- a) Medical morbidity – medical record review and questionnaire / participant self-reporting.
- b) Short Form (SF) -12 score  – self-administered questionnaire for quality of life.
- c) Additional cognitive function tests: the Symbol-Digit Modalities Test (SDMT) , the Hopkins Verbal Learning Test (HVLT-R)  and the Controlled Oral Word Association Test (COWAT) . These tests will then be performed in years 1, 3, 5 and 7 (close-out), in conjunction with the 3MS and CES-D, for confounding of depression and new onset depression – see Table 4.
- d) Height – measured, without shoes standing against a wall using a calibrated stadiometer. Measured again at Year 7 (or whenever the final annual visit occurs).
- e) Weight and waist circumference – measured following the removal of excess clothing and with calibrated scales. Waist circumference will be measured according to the NHANES III Protocol (<http://www.ncbi.nlm.nih.gov/books/bv.fcgi?rid=obesity.box.236>).
- f) Physical function testing – timed gait speed test for 3m (8ft)  and hand grip strength measured on a grip strength dynamometer.  Physical function testing will be performed in years 2, 4, 6 and 7 (close-out) – see Table 4.
- g) Concomitant medications, indication and year commenced – participant self-reporting, medical record review and family physician report.
- h) Medication compliance – the number of pills returned at this visit to the number expected with 100% compliance. Adequate adherence to placebo during the run-in period is an inclusion criterion for the study and is defined as pill count greater than 80% of those required to be taken during this phase. If considered necessary, the placebo run-in test for compliance may be repeated.
- i) Information on relevant clinical events.
- j) Retinal imaging – this will only be conducted on participants in Melbourne or other locations in Australia subject to the availability of imaging equipment. Consenting participants will have standardized non-mydratic retinal photography. After 5 minutes of dark adaptation, colour retinal photographs will be taken without pharmacological pupil dilation using Canon NMR 45 digital fundus cameras. Two retinal photographs, each

centered on the optic disc (ETDRS standard field 1) and macula (standards field 2) respectively, will be taken from both eyes. Images will be collected and archived in an image library. No analysis of the images will be carried out as part of ASPREE.

Participants' contact details will also be confirmed. In Australia, this will ensure the dispensing of study medication to the correct mailing address.

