### **3.2 Physical Performance**

Both performance-based and self-report instruments will be used to measure physical function. These detailed assessments will be carried out every other year, alternating with the cognitive assessment measures. Performance-based measures are very sensitive to change and can detect early decline prior to the onset of disability in activities of daily living (ADL). They have less of a ceiling effect than other measures of function or self-reported function and, as continuous variables provide more power to assess treatment effect. Small differences in performance (0.1 m/sec in gait speed) are related to important subsequent mortality risk, so that prevention of decline would represent an important treatment effect of aspirin. Self report of increased difficulty with an activity identifies early declines in performance measures, and incident mobility disability. Limitations in or inability to perform ADL and mobility tasks reflect the subject's perception of their ability to perform in their own environment, and correlate moderately with performance-based measures, and therefore are considered to be complementary. Self-report instrumental activities of daily living (IADL) disability measures assess ability to carry out functions such as cooking, shopping and taking medication, which are also important for maintenance of independent living.

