#### **a) Performance based measures**

Two performance-based measures will be used: grip strength and gait speed for usual

2258 walking. These two measures are each strong independent predictors of mortality and  
2259 disability, and very sensitive to change. Both can be assessed within 10 minutes and in  
2260 both the home or clinic settings.

2261 Hand grip strength will be measured in kilograms using a handheld isometric dynamometer  
2262 (Jaymar; JLW Instruments, Chicago, Illinois). Grip strength of the dominant hand will be  
2263 measured as the best of three trials. In the Women's Health and Aging Study, the mean  
2264 baseline grip strength was 19.7 ( $\pm$  5.9) kg, and declined by 1.4 ( $\pm$  4.3) kg, or 6.8% over 3 yrs  
2265.

2266 Gait speed will be assessed as the time in seconds to walk 3 meters (8 feet) at the  
2267 participant's usual walking pace from a standing start. Time on the faster of two walks will be  
2268 used to define scores. Gait speed will be examined as a continuous variable. A walking  
2269 speed lower than 0.42 m/s is considered to represent severe walking disability. Speeds  
2270 of less than 1.0 m/sec are predictive of mortality and hospitalization and changes of >0.1  
2271 m/sec related to significant perceived decline.

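### The gait course is given as both 3 m and 8 ft, which are different lengths; if the length walked is not the length used to compute speed, speed is overstated by 23.0% or understated by 18.7%

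*Protocol*

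**What the plan says.** The course is defined in two operative places.

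- Protocol section 7.1.3, item f (Visit 2 determinations, repeated at later visits): "timed gait speed test for 3m (8ft").
- Appendix 1, section 3.2 a): "Gait speed will be assessed as the time in seconds to walk 3 meters (8 feet) at the" participant's usual pace, keeping the faster of two walks.

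On analysis, Appendix 1, section 3.2 a), says: "Gait speed will be examined as a continuous variable". The same appendix supplies the yardsticks. Its section 3.2 ties "Small differences in performance (0.1 m/sec in gait speed") to later mortality risk. Section 3.2 a) describes changes above 0.1 "m/sec related to significant perceived decline". It also cites two reference speeds: speeds "of less than 1.0 m/sec are predictive of mortality and hospitalization", and a walking "speed lower than 0.42 m/s is considered to represent severe walking disability".

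Section 5.3 lists gait speed among the other measures, and section 1.2.4 calls it a tertiary outcome. Appendix 1, section 3.2 c), names it as one of the items that may be combined into a frailty assessment.

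**The concern.** Three metres and eight feet cannot both describe the same course. The figure sits in the measurement procedure itself, and the second statement repeats the first instead of correcting it. A site that marks out 3 m and a site that marks out 8 ft are both following the text.

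The recorded quantity is a time, and speed is a distance divided by that time. Any mismatch between the distance walked and the distance in the numerator therefore carries straight into the outcome as a multiplying factor. Gait speed was chosen to pick up early, subtle decline, and the protocol regards a difference of 0.1 m/s as important. A distance error that can exceed that amount weakens the measure for its stated purpose.

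**Working it through.** **Inputs.** Course length: 3 m and 8 ft (section 7.1.3 f; Appendix 1, section 3.2 a). Important difference: 0.1 m/s (Appendix 1, section 3.2). Reference speeds: 1.0 and 0.42 m/s (Appendix 1, section 3.2 a). Conversion: 1 ft = 0.3048 m by definition.

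**Step 1: does the stated equivalence reproduce?** No.

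- 8 ft = 8 × 0.3048 = 2.4384 m
- 3 m = 3 / 0.3048 = 9.84 ft
- Gap = 3 − 2.4384 = 0.56 m, too large for rounding on a course this short.

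**Step 2: relative error in speed.** Recorded speed = assumed distance / time, and time = distance walked / true speed. So recorded speed = true speed × (assumed distance / distance walked).

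- Walk 8 ft, compute with 3 m: 3 / 2.4384 = 1.230, an overstatement of 23.0%.
- Walk 3 m, compute with 8 ft: 2.4384 / 3 = 0.813, an understatement of 18.7%.

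**Step 3: absolute error against 0.1 m/s.** Error = true speed × 0.2303 (over) or × 0.1872 (under).

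| True speed (m/s) | Overstated by (m/s) | Multiple of 0.1 | Understated by (m/s) | Multiple of 0.1 |
|---|---|---|---|---|
| 0.42 | 0.097 | 0.97 | 0.079 | 0.79 |
| 0.60 | 0.138 | 1.38 | 0.112 | 1.12 |
| 0.80 | 0.184 | 1.84 | 0.150 | 1.50 |
| 1.00 | 0.230 | 2.30 | 0.187 | 1.87 |
| 1.20 | 0.276 | 2.76 | 0.225 | 2.25 |

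The error reaches 0.2 m/s at a true speed of 0.2 / 0.2303 = 0.87 m/s (over) or 0.2 / 0.1872 = 1.07 m/s (under). It reaches 0.1 m/s at 0.43 or 0.53 m/s.

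**Step 4: what each pattern of use would do.**

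- *Walked and assumed lengths agree at every visit:* no error, whichever length it is.
- *One course and one wrong divisor throughout:* a constant rescaling. A true change of 0.1 m/s reads as 0.1 × 1.230 = 0.12 or 0.1 × 0.813 = 0.08 m/s. Comparison with the cited reference speeds is distorted: a recorded 1.0 m/s would be a true 1 / 1.230 = 0.81 or 1 / 0.813 = 1.23 m/s.
- *Course or divisor differs between sites:* extra variation in pooled values.
- *Course or divisor differs between visits for one person:* a false change. For someone walking steadily at 1.0 m/s it would be 0.19 to 0.23 m/s.

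**The case against.** The strongest reply is that the text is sloppy but the practice may be sound. In both places metres come first with feet in parentheses, and every speed is quoted in m/s, which leans towards 3 m. Section 7.1.5 requires annual measurements to follow the same procedures as baseline. Section 13.2 promises SOPs covering all procedures in detail and training aimed at consistency between the two countries. Those SOPs are not part of the protocol and may fix the length. This stands: mixed use is a possibility, not something the protocol sets. The protocol text would still be wrong, and a requirement to repeat baseline procedures only points back to the same ambiguous course.

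A reader might also infer several stronger things that the protocol does not support:

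- *That participants would be misclassified at analysis cut-points of 0.42 and 1.0 m/s.* These are reference speeds from cited literature. The stated analysis is continuous, and the frailty combination is described only as something that can be done.
- *That home testing means a different course from clinic testing.* Appendix 1 says the test is feasible in either setting; it says nothing about different lengths.
- *That a false country difference would appear in a pre-specified subgroup.* Section 7.3.4 tests treatment-by-country interaction in Cox models and does not compare country levels. A scaling error common to a country multiplies both arms alike, so it cannot create an effect where there is none, though it would rescale a real one.
- *That the treatment comparison is biased.* Randomization is stratified by site (sections 2 and 7.1.4) and the trial is double-blind, so no directional bias between arms is expected.

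**Conclusion.** The point holds as a wrong figure in a measurement procedure. The conversion is certain, the contradiction appears in both operative places, and the protocol does not resolve it.

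The size is conditional. The errors of +23.0% and −18.7% arise only if the length walked differs from the length used to compute speed. Being about twice the 0.1 m/s yardstick is true near 1.0 m/s; at 0.42 m/s the error is at or just below that yardstick. False change within a person further requires a switch of course or divisor between visits. How often any of this happens cannot be read from the protocol, so a loss of power is possible but cannot be quantified.

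The reach is limited: a tertiary measure and a frailty input, with no effect on the primary or secondary endpoints or the sample size. It should be corrected, because the measure is a named outcome and the correction is cheap.

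**What to change.** 1. In section 7.1.3 f and Appendix 1, section 3.2 a), state one course length with its correct conversion: either 3 m (9.84 ft, about 9 ft 10 in) or 8 ft (2.44 m). The natural choice is whichever length sites have been marking out.
2. From now on, record the length walked on the CRF and compute speed from that recorded length.
3. For completed visits, confirm the length used, from the SOP or by asking each site, before speed is derived. A new CRF field cannot recover this: Appendix 2 already reports the recruitment numbers achieved, so baseline walks have been done.
4. If the query shows that more than one length was used, derive speed from the length that applied at each visit.

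Cost: two wording changes, one CRF field and one site query. The query is the larger part of the work, unless the SOP settles the matter.
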